**Methods:**

Protocol for a randomized crossover clinical trial. Women aged 18–65 years with a diagnosis of fibromyalgia will be included. Patients who have undergone resistance training in the last 6 months, who have another associated rheumatic disease, who have travel or scheduling commitments that will require them to be absent for the next 4 (four) weeks from the start of the study, who have upper and/or lower extremity musculoskeletal injuries, or who have cardiac problems that prevent maximal and submaximal exercise will not be included. The primary outcome will be preference. Secondary outcomes will be expectation, pain intensity, affect, and perceived effort, training volume, and cadence. For the primary outcome, the number of choices of the 3 types of training will be recorded as a percentage. For the analysis of the primary outcome, we will summarize the patient's preference in a contingency table, compare the proportions using the chi‐squared test, and finally verify the effect size of the observed differences. For the secondary outcomes, statistical analyses will be performed by a blind statistician. The independent variables of group and time will be considered for each dependent variable.

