### Randomization, Allocation, Blinding, Patient Timeline, and Data Collection Methods

2.5

Randomization will be performed before each training protocol, taking into account the 3 different types of training protocols. The order in which the patient will perform the training protocol will be determined by a simple draw in an envelope containing 3 papers described as 1 series, 2 series, or 3 series. Therefore, if in the first session the patient draws the paper described as 1 series, in the following week this paper will be removed from the envelope and the same will draw 2 or 3 series, and so on.

In this way, all patients involved in the study will randomly perform the 3 types of protocols proposed in the study, and they will be their own controls. To avoid allocation bias, opaque sealed envelopes will be used, with sequential numbers on the outside of the envelope. This allocation will be made by Researcher B, who will not be involved in any other study procedures. Patients selected in the screening conducted by Researcher A who agree to participate in the research will be randomly assigned.

Regarding blinding, all assessments will be performed by Researcher A, who will not be involved in the interventions and will not participate in the delivery of the training protocol. Each patient will remain identified by numbers and not by name. In order not to compromise the blinding of the study, all patients will undergo the same assessment before and after the training session. Due to the nature of the proposed intervention (physical exercise), the therapist and patients will not be blinded to the intervention. Patients will be instructed not to disclose any information to other patients and/or researchers.

At the end of the T3 training protocol, with a 7‐day interval between these assessments, we will conduct T4, where each patient will be asked which training protocol they prefer. After T4, researcher D will tabulate the data, which will be delivered to researcher E, who will be responsible for the statistical analysis and who will not participate in the previous phases of the research (Figure 2).

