**FIGURE 3 pri70101-fig-0003:**
[figure not shown]
Proposed exercises.

The T1 assessment will be performed respecting a 7‐day interval after the T0 assessment. At this interval, the patient will return and we will perform the first training protocol drawn on that day (T1). In addition, we will collect the following variables: pain intensity and affect before and after training, total training volume, and subjective effort after training.

The T2 and T3 assessments will follow the same procedure as T1, with a 7‐day interval between each protocol (T1, T2 and T3), so that the patient will perform the other two training protocols. The protocol draw will take place on the respective days of each assessment (T2) and (T3). If the envelope of the protocol drawn has already been performed on previous days, the patient will be instructed to perform a new draw.

Finally, at the T4 assessment, one week after the T3 assessment, the patient will be asked by telephone by the same evaluator (T0 baseline) about his preference for the programs performed in the study (with 1, 2 or 3 sets), standardizing the same commands used in person throughout the study. The following is a description of the three types of training programs with different volumes. The only different training variable will be the number of sets in the three training protocols of the study (Table 1).

**TABLE 1 pri70101-tbl-0001:** Training protocol.

Training (protocol)	Exercise	Sets (*n*)	Repetitions (*n*)	Load (1RM)	Rest (minute)
1	1–4	1	10	60%	2
2		2			
3		3			

*Note:* 1RM: One‐repetition maximum test. Each patient will receive the exercise session individually, as each of the three training protocols has different volumes (i.e., 1, 2, or 3 sets), consequently, the durations will vary for each patient; and then the durations will be compared between the groups.

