### Statistical Methods

2.18

For the primary outcome (preference), the number of choices of the 3 types of training will be recorded as a percentage. For the analysis of the primary outcome, we will summarize the patient's preference in a contingency table, compare the proportions using the chi‐squared test, and finally verify the effect size of the observed differences. For the secondary outcomes, statistical analyses will be performed by a blind statistician using commercial software. The independent variables of group and time (T0, T1, T2, T3, T4) will be considered for each dependent variable: pain intensity, subjective effort, affect and satisfaction. The Kolmogorov–Smirnov test was used to verify the distribution of the data and the Levene test was used to analyze the homogeneity of variance.

A mixed design analysis of variance will be conducted for the primary and secondary outcomes with a normal distribution, with time as the within‐subject factor and group as the between‐subject factor. If the data are not normally distributed, the Friedman test is used. Time × group interactions and between‐ and within‐group differences were analyzed for all variables. Finally, the Bonferroni test is used in post hoc analyses to determine whether there are differences between‐groups at different intervention times. A 5% significance level and 95% confidence interval will be used for all statistical analyses.

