## Results

3

Based on the design of this protocol, we intend to evaluate the preference of women with fibromyalgia in three different protocols in resistance training, evaluating these patients over 4 weeks where all of them will experience the three protocols. 7 days after the last week of the protocol, we will evaluate the patients' preference.

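### The planned mixed ANOVA treats the training protocols as between-subject groups, although every patient performs all three, so protocol main effects and single-time contrasts are tested against the wrong error term

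*Protocol article*

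**What the plan says.** The abstract describes the study as "Protocol for a randomized crossover clinical trial". Section 2.5 (Randomization) states that "all patients involved in the study will randomly perform the 3 types of protocols proposed in the study, and they will be their own controls", and section 3 (Results) repeats that "all of them will experience the three protocols".

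Section 2.18 (Statistical Methods) then sets a mixed-design ANOVA "with time as the within‐subject factor and group as the between‐subject factor" for normally distributed primary and secondary outcomes. It lists the levels of time as T0 to T4. It promises time-by-group interactions for all variables, Levene's test, and Bonferroni comparisons between groups at the different times. For the other case it says: "If the data are not normally distributed, the Friedman test is used".

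Section 2.18 does not define group. The article's one use of the word outside that section that shows its meaning is the note to Table 1 (section 2.6), where the groups are the set volumes: "the durations will be compared between the groups".

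**The concern.** A between-subject factor is one whose levels are filled by different people. Here each woman belongs to all three levels, so the stated model does not describe the data.

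A between-subject analysis of protocol handles one woman's three sessions as if three women had supplied them. Stable differences between patients, which a crossover is meant to remove, then stay in the error term. The comparisons at stake are pain, affect and perceived effort across volumes. These are what would explain the preference result, and section 2.16 says that patients will be told if one program proves superior. A test with far less power than the design offers could report no difference between volumes when there is one.

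Two further features of the paragraph do not fit the design:

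- **Time.** Its levels are visits. Each of T1, T2 and T3 delivers a different protocol to a given patient, and T0 and T4 deliver none. The pre, post and 24-hour points at which Table 2 collects pain and affect are not levels of the factor.
- **Fallback.** Friedman is a one-factor test for related samples. A normality check would therefore decide whether the data count as paired, and the paired branch cannot supply the promised interaction.

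**Working it through.** **The plan's own figure.** Section 2.17 gives w = 0.8, α = 0.05, power 0.80 and 25 degrees of freedom. At n = 36, λ = 36 × 0.8² = 23.04, the critical chi-squared is 37.65 and power is 0.804. At n = 35 power is 0.789. The 36 reproduces. It belongs to the preference test and does not depend on the point made here.

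**Inputs for the check.** There are 36 patients and three protocols (documents). The within-patient correlation ρ between sessions and a linear 0.5 SD spread from 1 to 3 sets are assumptions, because the article gives neither. The SD is set to 1.

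**One value per session (for example perceived effort).** Standard error of a difference between two protocols:

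- between-subject: √(2/36) = 0.236
- within-patient: √(2(1 − ρ)/36)
- ratio: 1/√(1 − ρ)

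Rejection rates come from 20,000 simulated trials per setting. They compare the between-subject F (2 and 105 df) with the repeated-measures F (2 and 70 df).

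| ρ | Within-patient SE | SE ratio | Null rejection, between / within | Power, between / within |
|---|---|---|---|---|
| 0 | 0.236 | 1.00 | 5.5% / 5.4% | 45% / 44% |
| 0.3 | 0.197 | 1.20 | 1.5% / 5.0% | 41% / 60% |
| 0.5 | 0.167 | 1.41 | 0.3% / 4.6% | 37% / 75% |
| 0.7 | 0.129 | 1.83 | 0.02% / 5.2% | 32% / 93% |

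**Three values per session (pre, post, 24 h).** A second simulation used 36 patients × 3 protocols × 3 times, with 5,000 runs. The patient share of variance was 0.5 or 0.7, with or without a shared day effect, and no patient had her own time course.

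- Protocol main effect under the null: the between-subject test rejects close to 0%.
- Time-by-group interaction under the null: 4.3–5.2% (mixed ANOVA) against 4.6–5.4% (repeated measures).
- Interaction power, 0.5 SD spread at one time point: 46.1% against 45.9%, 70.3% against 69.4%, 79.2% against 78.7%, and 96.4% against 96.2%.

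The interaction is unharmed because its error term already removes each session's level, and with it the stable patient differences. A loss would appear only if patients' change scores correlated across sessions.

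**Other readings of group.**

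- *Protocol received at a given visit:* each comparison rests on about 36/3 = 12 patients per protocol. The standard error is √(2/12) = 0.408, against 0.167 within patients at ρ = 0.5.
- *Sequence:* the article does not say this, and the group effect would then test order and not volume.

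Neither reading rescues the stated model.

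**The case against.** The strongest reply is that the damage is narrower than the wording suggests. Four parts of it stand.

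1. A reader might infer that every secondary protocol comparison is wrong. The working does not support that. The interaction keeps its size and power unless change scores correlate across sessions, and the inflation figures apply to one value per session.
2. A reader might infer that the plan has no period term. It has one in substance: the time factor runs over the visits, and T1 to T3 are the periods. The fault is that visit and protocol are entangled in that factor and within-session time is missing.
3. A reader might infer that the benefit expressed by "they will be their own controls" is lost throughout. The Friedman branch keeps the pairing, and pain, affect and effort are bounded rating scales that may well be sent there.
4. The article does not say that the sessions will be stacked as 108 independent records. That is one way of carrying out the stated model, and the figures are conditional on it.

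It can also be said that the error is conservative and that an analysis plan might correct it. The first is true and lowers the urgency. The second does not excuse the text, because the article states a specific model that contradicts its own design.

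**Conclusion.** The stated model is wrong for this crossover. If protocol is analysed between subjects, patient variance stays in the error term for protocol main effects, for between-group contrasts at a single time point, and for perceived effort.

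For one value per session, the standard error is 1.20 to 1.83 times too large over assumed ρ of 0.3 to 0.7. True type I error is about 1.5% or less at a nominal 5%. Power falls from between 60% and 93% to between 41% and 32% for an assumed 0.5 SD spread. At ρ = 0 nothing is lost. The direction holds for any positive correlation, but the documents do not fix the size.

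This should be fixed, though it does not threaten the trial's main result. A reader might infer that the primary analysis or the sample size is compromised, or that false positive findings are likely. The documents support none of these: preference has its own chi-squared analysis, the 36 rests on that test, and the error works mainly towards missed differences. Section 2.18 does extend the ANOVA to the primary outcome, which is a three-way categorical choice that an ANOVA cannot take. That wording should be corrected in the same edit.

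**What to change.** Rewrite the ANOVA paragraph of section 2.18 so that protocol is a within-patient factor:

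- For each secondary outcome, use a linear mixed model with fixed effects for protocol (1, 2 or 3 sets) and period (T1, T2, T3). For pain and affect, add within-session time and protocol × time.
- Include a random patient effect. Wherever a session contributes more than one value, also include a random patient-by-session effect. This term matters: with a patient effect alone and no baseline covariate, the protocol test rejected 26–28% under the null in simulations with a shared day effect (25% of variance with a patient share of 50%, or 15% with a patient share of 70%).
- If the pre-session value is used as a covariate, remove it from the outcome time levels.
- Take Bonferroni-adjusted within-patient protocol contrasts from this model.
- Drop Levene's test across groups, and do not promise an interaction from the Friedman test.
- State that the ANOVA does not apply to preference.

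The cost is the rewording of one paragraph. Standard software fits the model, and no new data, visits or patients are needed.

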### Pain Intensity

2.11

The intensity of widespread pain is assessed using the numerical pain rating scale, a self‐report instrument validated for Portuguese (Ferreira‐Valente et al. 2011). The Numeric Pain Scale has a sequence of numbers (from 0 to 10), where 0 represents “no pain” and 10 represents “the worst pain imaginable”. A reduction of 2 points in pain intensity is considered a minimal clinically important difference (Farrar et al. 2001). The numerical pain scale is answered by the patients at three time points: at the beginning, at the end, and 24 h after the end of each resistance training session.

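### The Friedman fallback has no interaction term, so on that branch the time × group interaction promised for all variables cannot be delivered for pain and affect as written

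*Protocol article*

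**What the plan says.** Section 2.18 of the protocol article sets up a two-branch rule for the secondary outcomes.

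- Gate: "The Kolmogorov–Smirnov test was used to verify the distribution of the data", with Levene's test for equal variances. The version of the test, the unit tested (each reading, pooled scores or residuals) and the rejection threshold are not given. The software is described only as commercial.
- If normal: "A mixed design analysis of variance will be conducted for the primary and secondary outcomes with a normal distribution". In that model group is taken as between-subject and time as within-subject.
- If not: "If the data are not normally distributed, the Friedman test is used".
- Then, for both branches: "Time × group interactions and between‐ and within‐group differences were analyzed for all variables". Bonferroni comparisons between groups follow.

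The variables named for analysis are "pain intensity, subjective effort, affect and satisfaction", with time listed as T0 to T4.

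Section 2.5 says that every patient performs all three protocols and serves as her own control. Sections 2.11 and 2.12 and Table 2 have pain (0 to 10) and affect (−5 to +5) read before, after and 24 h after each session. Table 2 gives perceived effort, training volume and cadence one value per session.

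**The concern.** The fallback and the promise do not fit together. Friedman's test compares k related measurements on one factor. It has no second factor, so it cannot separate the protocol from the time of reading and cannot test whether one modifies the other. The promise of interactions makes no exception for this branch.

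For pain and affect, the measurement schedule bears directly on whether the change over a session differs with the number of sets, which is a protocol × reading interaction. An analyst who follows the text on the Friedman branch must either leave the interaction out or devise a step after seeing the data. If Friedman is applied to all readings together, a significant result may show only that scores move after any exercise, and it could be reported as an effect of volume.

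Two further parts of the rule assume independent groups: Levene's test and the between-subject group factor. Here the same patients supply all three conditions.

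**Working it through.** **Inputs from the article.** Three protocols; three readings per session for pain and affect (2.11, 2.12, Table 2); n = 36 (2.17); 5% significance level (2.18). Section 2.17 reproduces as stated: λ = 36 × 0.8² = 23.04 and, with 25 degrees of freedom, critical value 37.65 and power 0.804. It serves here only as the source of n.

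**Assumptions, not from the article.** Integer scores cut to 0–10, mean 6, SD 2, equal correlation 0.6 between a patient's nine readings; 1,500 simulated trials per setting unless noted.

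**Step 1: what each test can estimate.** Three protocols × three readings give nine cells and 9 − 1 = 8 degrees of freedom between cells. These split into protocol (2), reading (2) and interaction (2 × 2 = 4). Friedman's statistic, before correction for ties, is

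Q = 12 / [n k (k + 1)] × Σ Rⱼ² − 3 n (k + 1), on k − 1 degrees of freedom,

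where Rⱼ is the rank sum of condition j. With k = 9 it is one test on 8 degrees of freedom, with all three sources mixed. With k = 3 (three protocols at one reading, or three readings in one protocol) it tests one factor at a fixed level of the other. Neither is an interaction test.

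**Step 2: can the gate send pain to Friedman?** Share of simulated trials in which normality is rejected, with no effects present:

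| Version of Kolmogorov–Smirnov | One reading | At least one of nine |
|---|---|---|
| Uncorrected (sample mean and SD used as if known) | about 2% | about 17% |
| Lilliefors correction | about 57% | over 99% |

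For affect (assumed mean 2, SD 2; 2,000 runs) Lilliefors rejects one reading in 62%. The underlying variable is normal in every run, so the high Lilliefors rates come from integer scoring.

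**Step 3: what Friedman would show.** Take a common effect of time and no protocol difference, so the true interaction is zero.

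- Friedman over nine readings, +1 point after the session only: significant in 99.8% of runs.
- The same test, +1 after and +0.5 at 24 h (1,000 runs): 98%.
- Within-patient repeated-measures ANOVA, interaction F = (SS_int / 4) / (SS_err / 140), with 4 × 35 = 140 error degrees of freedom: 5.9%, close to the nominal 5%.
- Friedman across the three protocols on each patient's post-minus-pre change: 5.6%, also close to nominal.

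With a true interaction of −0.7, 0 and +0.7 points after 1, 2 and 3 sets, Friedman on changes has 67% power and the within-patient ANOVA 80%. That ANOVA treats protocol as a within-patient factor, which is not the mixed design that section 2.18 describes.

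**Step 4: which outcomes are affected.** Pain and affect have a within-session interaction. Perceived effort, training volume and cadence, with one value per session, have none on either branch, so the promise for all variables cannot apply to them in that form.

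**The case against.** Much of the case on the other side stands.

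- A reader might infer that the trial's key secondary contrast is untestable. The article ranks no secondary contrast, and the secondary questions stated in its abstract and section 5 are whether preference relates to exertion and to pain. Nor is the contrast untestable in principle: because every patient performs all protocols, Friedman on within-patient changes would test it at the right level. The fault is that no such step is stated.
- The article does not say that Friedman will be run over nine readings, so the 98% to 99.8% describes one possible reading of the plan.
- A reader might also infer that the branch depends on the software and not on the data. It depends on both: with Lilliefors a single reading fails in some runs and passes in others. The figure above 99% needs a rule that any one failing reading triggers the switch, and no such rule is given.
- The rounding argument covers pain and affect only. Perceived effort may be given in decimals, volume is a product and cadence is a stopwatch time.
- Section 2.18 lists time as T0 to T4, not as before, after and 24 h. That leaves the promised interaction less clear, but Friedman has one factor under either definition.
- The article does not say that raw scores rather than residuals are checked, so that criticism would be inference.

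A condensed article may leave the unit of analysis to a full plan. That does not dispose of the point: two adjacent sentences commit to a test and to a result that the test cannot produce. Nor is the ANOVA branch a safe alternative, since it treats group as a between-subject factor.

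**Conclusion.** The rule is wrong as written. On the Friedman branch the promised interaction for pain and affect cannot be obtained from the named test, and no step is given that would obtain it. This follows from the structure of the test and needs no assumed figures.

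How often the branch would be taken does rest on assumptions. For one reading it is about 2% or about 57%, depending on the version of the normality test. These figures assume integer scores, mean 6, SD 2 and n = 36; the Friedman and nine-reading figures also assume a correlation of 0.6. The risk of mistaking a time effect for a volume effect applies if all readings are pooled.

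Levene's test and the between-subject group factor do not suit a design in which patients are their own controls, so the ANOVA branch needs correction too. The point concerns secondary outcomes only; the chi-squared analysis of preference does not depend on it. It should be corrected before the data are analysed.

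**What to change.** Delete the Kolmogorov–Smirnov and Levene gate and the switch to Friedman, and pre-specify one analysis per outcome.

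- **Pain and affect:** a linear mixed model with protocol (1, 2, 3 sets), reading (pre, post, 24 h), protocol × reading and period as fixed effects, and patient and session within patient as random effects. The protocol × reading term is the stated test.
- **Perceived effort, training volume and cadence:** protocol and period as fixed effects and patient as a random effect, with no interaction.
- **If residuals are poor:** keep the same terms and use bootstrap intervals or an ordinal mixed model. At minimum, state that Friedman will be applied to within-patient changes across the three protocols.

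This also removes the between-subject group factor. The cost is revised wording and slightly more analysis work; no new data are needed.

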### Affect

2.12

The affective valence scale will monitor pleasure or displeasure during the three resistance training programs and will be conducted using the affective valence scale. The scale is quantified as follows: +5 to −5, corresponding, respectively, to the two antagonistic descriptors of the feeling during physical exercise and/or physical activity, which can be: “very good” and “very bad”. In addition, the affective valence scale presents other intermediate descriptors, which are: +3 = good, +1 = fairly good, 0 = neutral, −1 = fairly bad, and −3 = bad (Hardy and Rejeski 1989). The affective valence scale is completed by the patients at three times: at the beginning, at the end, and 24 h after the end of each resistance training session.

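### Pain and affect are read before every session, but the planned analysis uses no covariate, so precision is lost on these two secondary outcomes

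*Protocol article*

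**What the plan says.** Section 2.18 (Statistical Methods) fixes the method: "A mixed design analysis of variance will be conducted for the primary and secondary outcomes with a normal distribution". The same sentence goes on to assign the two factors: "with time as the within‐subject factor and group as the between‐subject factor". A Friedman test replaces the ANOVA when the data are not normal. The factors are introduced by "The independent variables of group and time (T0, T1, T2, T3, T4) will be considered for each dependent variable", and the list that follows includes pain intensity and affect. The comparisons are then given as "Time × group interactions and between‐ and within‐group differences were analyzed for all variables". As a last step, "the Bonferroni test is used in post hoc analyses to determine whether there are differences"; these are comparisons of the groups at the various times. Neither the ANOVA nor its fallback has a covariate.

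The readings themselves are described elsewhere. For T1, section 2.6 lists "pain intensity and affect before and after training, total training volume, and subjective effort after training", and T2 and T3 repeat the procedure. Section 2.11 states for pain: "The numerical pain scale is answered by the patients at three time points: at the beginning, at the end, and 24 h after" (counted from the session's close). Section 2.12 states for affect: "The affective valence scale is completed by the patients at three times: at the beginning, at the end, and 24 h after" (counted likewise). Table 2 marks both variables in the pre, post and 24 h columns of each of T1, T2 and T3. Each patient therefore supplies three pre-session readings of pain and three of affect, one for each protocol performed.

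**The concern.** Pain and affect vary from week to week within a patient. A patient who arrives in more pain than usual will tend to leave in more pain than usual, whichever number of sets was drawn. The pre-session reading measures that fluctuation. Used as a covariate, it takes the predictable part out of the protocol contrast.

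The stated method does not do this. If the reading is a level of the time factor, the interaction compares raw changes and carries the full noise of the pre reading. If the reading is left out, the post readings are compared with the session-to-session fluctuation still in them. Comparing patients with themselves does not remove the problem. Patient effects absorb stable differences between patients, but not differences between one patient's sessions. The single T0 pain reading cannot help either, because it is constant across a patient's three sessions.

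At stake is the width of the intervals for the volume contrasts on pain and affect. These show whether more sets worsen symptoms. Section 2.16 says that patients will be told if one program proves superior, and the sample size was not set with these outcomes in view.

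**Working it through.** **The plan's own figure.** Section 2.17 gives w = 0.8, α = 0.05, 25 degrees of freedom and power 0.80 (printed as β). Then λ = 36 × 0.8² = 23.04, the critical value is 37.65 and the power is 0.804, so 36 is reproduced. No input concerns pain or affect, so this point does not change N.

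**Inputs for the check.** From the documents: 36 patients, three sessions each, and a pre, post and 24 h reading per session. Assumed, because the article gives neither an SD nor a correlation: the correlation r between pre and post readings of the same session after patient means are removed, and equal pre and post variances σ².

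**Formulas.** For the difference between two protocols over n patients, the variance is (2σ²/n) × v, where:

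- post alone: v = 1
- change from pre: v = 2(1−r)
- post with pre as covariate: v = 1−r²

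The covariate/change ratio is (1−r²) / [2(1−r)] = (1+r)/2. The covariate/post ratio is 1−r².

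| r (assumed) | change, v | covariate, v | covariate/change | covariate/post | patients matching 36 on change |
|---|---|---|---|---|---|
| 0.3 | 1.40 | 0.91 | 0.65 | 0.91 | 36 × 0.65 = 23.4 |
| 0.5 | 1.00 | 0.75 | 0.75 | 0.75 | 27.0 |
| 0.7 | 0.60 | 0.51 | 0.85 | 0.51 | 30.6 |
| 0.9 | 0.20 | 0.19 | 0.95 | 0.19 | 34.2 |

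The ordering does not depend on equal variances. Change fixes the slope on the pre reading at 1 and post-only fixes it at 0. The covariate model estimates the slope that leaves the least residual variance.

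**Simulation.** With 36 patients, three sessions and 4,000 runs per r, the covariate/change ratios were 0.68, 0.75, 0.88 and 0.97. The covariate/post ratios were 0.90, 0.77, 0.52 and 0.18. With random order, period effects and 6,000 runs, they were 0.67, 0.77, 0.87 and 0.96, and 0.92, 0.76, 0.51 and 0.19. Covariate/change tends to lie slightly above the formula, which is the price of estimating one slope. At r = 0, where the covariate has nothing to offer, covariate/post was 1.015.

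**Illustration.** Assume σ = 1.5 and a true 1-point difference, tested two-sided at 5% without Bonferroni. At r = 0.3 the standard error on change is 1.5 × √(2 × 1.40/36) = 0.418, and with the covariate 1.5 × √(2 × 0.91/36) = 0.337. Power on change against covariate is 0.67 vs 0.84 at r = 0.3, 0.81 vs 0.90 at r = 0.5 and 0.96 vs 0.98 at r = 0.7. Post alone gives 0.81 throughout.

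**The case against.** The strongest reply is that the criticised model is not written down. Section 2.18 defines time by visits T0 to T4 and never says how the pre, post and 24 h readings within a visit enter. A reader might infer that the plan definitely compares change scores. The text does not support that. It leaves open a change contrast or a post-only contrast, and the conclusion has to hold for both. It does, by the two ratio columns above.

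A reader might also infer that the Bonferroni correction is partly spent on pre-session comparisons that cannot be true effects, with a family of 9 (three pairs at three times, per-test level 0.0056) that should be 6 (0.0083). This too goes beyond the text, because no such family is defined. Nor is a pre-session difference null by construction. The draw is made on the session day (section 2.6) and patients are not blinded (section 2.5). If the reading follows the draw, knowing the number of sets could already shift affect or pain. The same fact limits the remedy, since a covariate read after the draw could itself be influenced by allocation.

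Third, choosing a covariate for secondary outcomes can be called detail for an analysis plan. That would hold if the protocol were silent. It instead states a method, and following it loses precision.

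What stands is that the loss is one of efficiency only, that its size rests on an unknown r, and that the same sentences contain a larger fault. They declare group a between-subject factor although every patient performs all three protocols.

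**Conclusion.** The point holds as a modest loss of precision on two secondary outcomes. The stated analysis makes no covariate use of a reading that is collected anyway. Apart from the small cost of one slope, covariate adjustment is at least as precise as either way of reading the plan. Against change, the variance saving is 35%, 25%, 15% and 5% at r = 0.3, 0.5, 0.7 and 0.9. Against post alone it is 9%, 25%, 49% and 81%. One saving is small where the other is large, so no value in this range makes adjustment pointless under both readings.

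These figures assume equal pre and post variances and a value of r that the documents do not supply. A reader might take the point to mean that the pain and affect results would be biased or that error rates would be inflated. The lack of a covariate does neither, because change and post-only contrasts are both valid in a randomised crossover. Correcting the between-subject factor alone would not recover the loss, so the two changes belong in one rewrite.

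**What to change.** When section 2.18 is corrected to a within-patient crossover model, make these changes for pain and affect:

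- Analyse the post reading and the 24 h reading each in a model with patient, period, protocol and that session's own pre reading as covariate.
- State that the Bonferroni comparisons are the three protocol pairs at post and at 24 h, with none at pre.
- State in section 2.6 that the pre reading is taken before that day's draw is opened, so that the covariate precedes allocation.

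No new measurement is needed. The cost is one extra parameter per model and a fixed order of assessment and draw on the session day. That order is a small procedural commitment on site as well as a change of analysis wording.
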